### Data collection

Data will be collected at clinic visits in the hospital where participants receive their usual care, and from the EMR system. Table 3 describes the study outcomes of the key three research appointments, including when and how those outcomes will be evaluated. The baseline assessment will be conducted at approximately 10 weeks’ gestation (between 8^+ 0^ and 13^+ 6^ weeks) from April to August 2024 for both the intervention and the control groups. Follow-up assessments will be conducted at approximately 26 weeks’ gestation (between 24^+ 0^ and 27^+ 6^ weeks); 34 weeks’ gestation (between 32^+ 0^ and 35^+ 6^ weeks); delivery (within 1 week after delivery); 42 days postpartum (6–8 weeks after delivery); 6 months postpartum (24–32weeks after delivery) and 12 months postpartum (48–56 weeks after delivery). Two well-trained key members of the project will be responsible for the collection, supervision, and management of data.

**Table 3 Tab3:** Outcome measurements for the HGWG-pro study

Outcomes	8^+ 0^−13^+ 6^ weeks’ gestation	24^+ 0^−27^+ 6^ weeks’ gestation		32^+ 0^−35^+ 6^ weeks’ gestation		Device (Manufacturer, model)		Methods
Anthropometric measures								
Height	√					Upright Posture Height and Weight Measuring Instrument (Shanghe Technology SH-200)		Measured to the nearest 0.5 cm at least twice without wearing shoes.
Weight	√	√		√		Upright Posture Height and Weight Measuring Instrument (Shanghe Technology SH-200)		Measured to the nearest 0.1 kg at least twice through wearing light-weight clothing without shoes.
Systolic and diastolic blood pressures	√	√		√		Fully Automatic Electronic Blood Pressure Monitor (Kentairou HBP-9020)		Measured to the nearest 1 mm Hg at least twice
Body composition	√	√		√		Bioelectrical impedance (BIA) TANITA MC-780MA		According to the standard procedure
LMP and Gestational age	√							Confirmed by ultrasounds conducted before the baseline survey clinic visit and extracted from EMR
Pre-pregnancy weight	√							Self-reported by women and extracted from EMR, if pre-pregnancy weight is not available, the earliest pregnancy weight measured before 10 weeks’ gestation will be obtained.
Behavioral measures and other measures								
Attitude and knowledge about GWG and weight management	√	√		√		Attitude and knowledge about gestational weight gain and weight management measured by 8 items, which was designed based on published articles [26, 27]. For example, women’s perceived weight category, realization about the importance of knowing recommended weight gain during pregnancy, knowledge about the best amount of weight to gain in pregnancy, dangers of excess weight gain for mother and child, et al. Corresponding options will be set according to the content of the question. Women could finish the questionnaire at the clinic or take it home.		
Food intake	√	√		√		Dietary intake will be measured by food frequency questionnaire (FFQ) investigating the frequency of food consumption over the past one month[28]. Women should finish the questionnaire under the guidance of the trained staff.		
Dietary behavior	√	√		√		Dietary behavior will be measured by self-designed questionnaire to achieve the frequency of unhealthy dietary behaviors and it was designed according to our health education goals based on published articles [29, 30]. It includes the frequency of overeating, sugary beverages, fried foods, unhealthy snacks, Western fast food, ordering takeout, high-sugar desserts, and processed meats.		
Physical activity	√	√		√		Physical activity will be measured by International Physical Activity Questionnaire-Short Form (IPAQ-SF) [31]. It asks about the frequency and duration of various types of physical activities over the past 7 days. The metabolic equivalent (MET) for different types of activities will be calculated as below and the higher score means the higher physical activity level: walking MET-minutes/week = 3.3 × walking minutes × walking days; moderate MET-minutes/week = 4.0 × moderate-intensity activity minutes × moderate-intensity activity days; vigorous MET-minutes/week = 8.0 × vigorous-intensity activity minutes × vigorous-intensity activity days; total physical activity MET-minutes/week = walking + moderate + vigorous MET-minutes/week.		
Sleep quality	√	√		√		Sleep quality will be measured by Pittsburgh Sleep Quality Index (PSQI) [32]. The score ranges from 0 to 21 and the higher score indicates the higher sleep quality.		
Quality of life	√	√		√		Quality of life will be measured by 12-Item Short Form Survey (SF-12) [33]. The score ranges from 0 to 100 and the higher score indicates the higher quality of life.		
Depression	√	√		√		Depression will be measured by 9-item Patient Health Questionnaire (PHQ-9) [34, 35]. The score ranges from 0 to 27 and the higher score indicates higher level of depression. A score greater than 4 indicates depression.		
Anxiety	√	√		√		Anxiety will be measured by Zung’s Self Rating Anxiety Scale (SAS) [36]. The score ranges from 25 to 100 and the higher score indicates higher level of anxiety. A score greater than 49 indicates anxiety.		
Social support	√					Social support will be measured by Maternity Social Support Scale (MSSS)[37], the score ranges from 5 to 30 and the higher score indicates higher level of social support.		
Self-efficacy	√	√		√		Self-efficacy will be measured by General Self-Efficacy Scale (GSES) [38, 39]. The score ranged from 10 to 40 and the higher score indicates higher level of self-efficacy.		
The stage of gestational weight control behavior	√	√		√		The investigators will use two items to assess it. “Have the participants started to adjust their diet/physical activity to control their weight during pregnancy?“, “No and I do not plan to do so in the next 6 months/No, but I am ready to start within the next 6 months/No, but I am ready to start in the next 30 days/Yes, but not regularly/Yes, I am currently controlling my weight by adjusting my diet/physical activity regularly, but it has not reached 6 months/Yes, I have been controlling my weight for more than 6 months by adjusting my diet/physical activity” choices will be provided.		
Clinical outcomes								
Gestational Diabetes Mellitus (GDM)		√				75 g 2-hour oral glucose tolerance test (OGTT), Fasting blood, Venous blood diagnosed according to International Association of Diabetes and Pregnancy Study Group (IADPSG) criteria: Fasting plasma glucose (FPG) ≥ 5.1 mmol/L, and/or 1-h blood glucose ≥ 10.0 mmol/L, and/or 2-h blood glucose ≥ 8.5 mmol/L		
Preeclampsia/ Gestational hypertension		√		√		Preeclampsia was defined according to the criteria of the American College of Obstetricians and Gynecologists (ACOG) i.e. systolic blood pressure of ≥ 140 mmHg or diastolic blood pressure of ≥ 90 mmHg occurring after 20 weeks of gestation in a previously normotensive woman combined with new-onset proteinuria of ≥ 0.3 g/24 h. Gestational hypertension was defined similarly but without the presence of proteinuria.		

At the baseline and all follow-up visits before delivery, anthropometric measures including height, weight, systolic and diastolic blood pressures, and body composition will be collected by the trained members of the project using the same device according to the standard methods. The date of the last menstrual period (LMP) and gestational age will be confirmed by ultrasounds conducted before the baseline clinic visit and extracted from EMR. Pre-pregnancy weight will be extracted from EMR, which was collected by women’s self-report. These indicators will be used to calculate BMI for initial assessment of eligibility.

We will use questionnaires to measure women’s behaviors (food intake, dietary behavior, physical activity, sedentary behavior, average steps during the last week), and other potential mediators of the intervention effect (e.g., attitude and knowledge about EGWG, stage of readiness) for behavioral change related to gestational weight control, social support, self-efficacy, frequency of weighing at three timepoints.

The cardiometabolic markers measured in women’s laboratory tests included levels of glucose, total cholesterol, triglycerides, high-density lipoprotein (HDL), low-density lipoprotein (LDL) during routine prenatal check-ups in the early, middle and late stages of pregnancy, and results of a 75 g 2-hour oral glucose tolerance test (OGTT) will be obtained from EMR. Women’s fasting blood samples at 8^+ 0^ to 13^+ 6^, 24^+ 0^ to 30^+ 6^, and 34^+ 0^ to 37^+ 6^ weeks’ gestation will be collected to measure levels of insulin, HbA1c, et al. Urine samples at three appointments and cord blood at birth will be collected for further analyses.

#### Measures about mother and infant 

women’s weight, blood pressure before delivery, infants’ gestational age at birth, birth weight, recumbent length at birth, Apgar scores, et al. will be obtained from EMR at one week after delivery. Maternal postpartum weight, and infants’ height, weight, head circumference at 42 days, 6 months and 1 year after delivery will be obtained through routine physical examination or telephone follow-up.

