### Randomization

The study will obtain informed consent at the baseline clinic visit at 8^+ 0^ to 13^+ 6^ weeks’ gestation. Only those women who meet the inclusion criteria, consent and complete the baseline assessment will be randomly assigned to either intervention or control group.

The 100 participants from each hospital will be randomly allocated at a 1:1 ratio to either the intervention group or the control group by the study staff, stratified by the categorical variables of age (< 30 and ≥ 30 years), pre-pregnancy BMI (< 28 and ≥ 28 kg/m^2^), and history of delivery with randomly determined block sizes of 4. Neither the staff nor the participants will be blinded to the group assignment due to the nature of the intervention program. The process of the randomization will be supervised by another study staff and recorded in a Microsoft EXCEL database.

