### Control group

Pregnant women randomized to the control group in the two hospitals will not receive any of the HGWG-pro intervention components and will continue their routine antenatal care according to the local hospital’s health care provision.

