Weight management	(1) Weight gain goal reminding: weight gain goal per week/during the whole pregnancy and current total weight gain will be displayed at the top of the weight record page. (2) Weight monitoring: participants will be asked to record their weight at least one time per week, with the weighing condition of fasting in the morning, emptying urine and feces, and wearing light clothes. All participants in the intervention group will be provided with a weighing scale. (3) Feedback about weight gain: as soon as participants input the current weight, the platform will immediately pop up feedback about weight gain by comparing with last week’s weight.

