In addition, pre-specified secondary outcomes also include changes of blood pressure, body fat percentage (%), fat free mass (kg), muscle mass (kg), attitude and knowledge, dietary intake, physical activity, sleep quality, quality of life, self-efficacy score, stage of change related to gestational weight control behavior, and incidence of depression and anxiety, which will be assessed from baseline (8^+ 0^−13^+ 6^ weeks) to midterm (24^+ 0^−27^+ 6^ weeks), and from baseline (8–14 weeks) to terminal (32^+ 0^−35^+ 6^ weeks). Incidence of postpartum weight retention, absolute/mean offspring weight, height, and head circumference will also be evaluated at 42 days, 6 months, and 12 months after delivery.

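### Postpartum weight may be measured at an examination or reported by telephone with no rule for which; because only one arm was given a scale and weighing conditions, self-reported values can carry arm-dependent error

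*Protocol article*

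**What the plan says.** All references are to the protocol article.

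- **Postpartum follow-up.** Measures about mother and infant covers "Maternal postpartum weight, and infants’ height, weight, head circumference at 42 days, 6 months and 1 year after delivery" and says that these "will be obtained through routine physical examination or telephone follow-up". It gives no order of preference between the two routes. The wording is the same for both arms.
- **Outcome affected.** Outcomes lists as secondary: "Incidence of postpartum weight retention, absolute/mean offspring weight, height, and head circumference will also be evaluated at 42 days, 6 months, and 12 months".
- **Intervention arm.** The weight management row of Table 2 says: "All participants in the intervention group will be provided with a weighing scale". It asks for a recorded weight at least weekly, "with the weighing condition of fasting in the morning, emptying urine and feces, and wearing light clothes". These conditions belong to self-monitoring in the app.
- **Control arm.** Under Control group, these women "will not receive any of the HGWG-pro intervention components", so they get neither the scale nor the weighing conditions.
- **Blinding.** Randomization states: "Neither the staff nor the participants will be blinded to the group assignment".
- **Contrast before delivery.** Data collection and Table 3 have weight at the three pregnancy visits taken by trained project staff on one named instrument, in light clothing without shoes, in both arms.

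**The concern.** Before delivery, weight is measured in one way for everyone. After delivery a second, looser route opens. If a telephone weight is what the woman reads from a home scale or remembers, its quality depends on what she has at home and how she was asked to weigh. The trial itself makes that differ by arm: one arm received a scale and months of weekly weighing under stated conditions, the other received neither. Lack of blinding adds a second route. Women who were counselled about weight may report it differently, and Fidelity/quality control says that the same two team members deliver the intervention and collect the data. The article does not say who makes the postpartum calls.

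Error that depends on allocation does not average out with more women, and adjusting for baseline does not remove it. If the source of each value is not recorded, it cannot be examined afterwards either. The Abstract presents follow-up to 12 months postpartum as a distinguishing feature of the trial, so weight retention will be read closely.

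**Working it through.** The plan states no figure on this point, so there is nothing to reproduce. The check sets the statements side by side and then illustrates size under declared assumptions.

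**Step 1: can error depend on arm?**
- Value measured at a routine examination: neither the study scale nor the weighing conditions enter. No arm-dependent error from this source.
- Telephone call that relays a value already recorded at an examination: the same.
- Telephone call that yields a home or remembered weight: an intervention woman may have used the study scale and the conditions she was asked to follow; a control woman was given neither. Arm-dependent error is possible.

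The article permits the third case and does not say how often it will occur.

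**Step 2: size, for illustration.** Let *p* be the share of weights that are self-reported by telephone, taken as equal in both arms, and δ the between-arm difference in mean self-report error. The spurious difference in mean retained weight is

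D = p × δ.

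The document gives neither *p* nor δ. Assumed ranges are *p* from 0 to 1 and δ of 0.5 to 1.5 kg in absolute value, with the sign left open.

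For the false-positive rate with no true effect, take n = 200/2 × 0.90 = 90 per arm. The total of 200 and the 10% attrition are from Sample size estimation; applying that attrition to the postpartum visits is an assumption. The SD of retained weight is assumed to be 4 or 6 kg. Then

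SE = SD × √(2/90) = 0.596 kg (SD 4) or 0.894 kg (SD 6),

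rate = Φ(|D|/SE − 1.96) + Φ(−|D|/SE − 1.96).

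| p | δ (kg) | D (kg) | rate, SD 4 | rate, SD 6 |
|---|---|---|---|---|
| 0 | any | 0 | 5% | 5% |
| 0.25 | 0.5 | 0.125 | 5.5% | 5.2% |
| 0.50 | 1.0 | 0.50 | 13.4% | 8.6% |
| 0.75 | 1.0 | 0.75 | 24.2% | 13.4% |
| 1.00 | 1.5 | 1.50 | 71.1% | 38.9% |

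The consequence thus runs from nothing to serious, depending on two quantities that the trial could record but the article does not fix.

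**Step 3: what the illustration does not cover.** Outcomes names the incidence of weight retention, a proportion. A shift in kilograms moves some women across whatever threshold defines it, but how many depends on that threshold and on the distribution around it. The table describes a comparison of means only.

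**The case against.** The strongest reply is that the article treats the arms alike. Both routes are open to both arms, and nothing says that one arm will be telephoned more often. A reader might infer that retention is measured differently in the two arms. The text does not support that; it supports only that it can be.

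Three further inferences also go too far.

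- **That telephone weights come from the study scale.** The scale and weighing conditions serve app self-monitoring in a programme that ends by 35+6 weeks. The 12-month window opens 48 weeks after delivery, so roughly a year after the programme ends. Continued use of the scale is possible but not stated. The in-person training covers the app and the wristband, so the women were asked, not trained, to weigh in this way.
- **That the error favours the intervention.** A fasting weight in light clothes would tend to read lower, but a control woman's remembered weight may also be too low. The sign is open.
- **That mothers will measure infant length and head circumference themselves.** A call may simply collect what the health-examination record shows.

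It is also fair to say that call scripts and source fields are commonly left to a fuller protocol, and that only secondary outcomes are touched. These replies limit the claim. They do not remove it: the article itself states an open choice of route, equipment and weighing conditions for one arm only, and no blinding. Together these leave room for arm-dependent error.

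**Conclusion.** The point holds as a possibility that the plan leaves open, not as a demonstrated bias. Self-reported telephone weights can carry arm-dependent error in postpartum weight retention at all three postpartum visits. Direction and size cannot be determined from the document. A reader might be tempted to quote a specific false benefit in kilograms, or to set it against the 2.19 kg anticipated for late pregnancy. Neither is supported: the telephone share and the reporting error are both assumed, zero is within the range, and 2.19 kg refers to a different outcome. The middle case above (0.5 kg, with a false-positive rate of about 9% to 13%) shows only why the source of each value is worth controlling.

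The clinic weights at 24–27 and 32–35 weeks, on which the primary outcomes rest, are taken by staff on the same device in both arms and are not affected.

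**What to change.** - Make the examination-recorded value the preferred source in both arms. When telephoning, ask first for the recorded value and its date, including infant length and head circumference.
- Where a home weight must be used, read the same weighing instruction to both arms.
- Record the source of every postpartum value and report the sources by arm at each visit.
- Keep all randomised women in the main intention-to-treat comparison, and add a sensitivity analysis limited to examination-measured values.

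The main comparison should not itself be restricted to examination values. Attendance is decided after randomisation and may differ by arm, so that would exchange a possible measurement bias for a possible selection bias and sit badly with the intention-to-treat principle in Statistical analyses.

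The cost is one extra form field, a short call script and one extra analysis. The sensitivity analysis will rest on fewer women and carries the selection risk just described, so it should be read beside the main result and not in place of it.

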#### Sociodemographic characteristics and outcomes 

Participants’ sociodemographic characteristics including age, educational level, occupation, socio-economic status (health insurance, household income last year), smoking and alcohol consumption, medical and reproductive history will be assessed at the baseline survey at 8 to 13^+ 6^ weeks’ gestation. Other outcomes including sleep quality, quality of life, and mental health, et al.

### Adverse events

The perinatal adverse outcomes, including pregnancy loss, gestational diabetes, pregnancy-induced hypertension, preeclampsia, cesarean delivery, and preterm birth (before 37 weeks) will be obtained from the EMR.

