### Eligibility and recruitment

The HGWG-pro study will recruit 200 overweight or obese pregnant women from 2 hospitals, with 100 participants from each hospital. Overweight or obesity were determined based on BMI recommendations of the Group of China Obesity Task Force of the Chinese Ministry of Health (overweight: 24 ≤ BMI < 28 kg/m^2^; obese: BMI ≥ 28 kg/m^2^) [22]. Pregnant women receiving usual antenatal care at the two hospitals will be firstly identified through gestational weeks. Only those at 8–14 weeks’ gestation will be further evaluated according to the inclusion criteria: aged between 18 and 40 years, pre-pregnancy BMI between 24 and 40 kg/m^2^ based on weight self-reported and recorded in the electronic medical record (EMR), singleton pregnancy, skilled at using smartphones and WeChat (mobile application), planning to attend regular antenatal care and delivery at Weifang Maternal and Child Health Hospital of Shandong or Tongzhou Maternal and Child Health hospital of Beijing, no contraindications to physical activity according to Physical Activity Readiness Questionnaire (PAR-Q), willing to be randomized and cooperate with regular follow-up visits and sign informed consent.

Exclusion Criteria including women with pre-pregnancy hypertension, severe cardiovascular or cerebrovascular diseases, respiratory disease, hepatic or renal disease, malignant tumors, systemic lupus erythematosus, thyroid disease, severe anemia, and other chronic diseases, cervical insufficiency, multiple pregnancy, continuous vaginal bleeding, diabetes before pregnancy, special dietary needs (e.g. vegetarianism), severe psychiatric disorders, with a history of bariatric surgery or other surgical history involving important organs within 3 months; participated in other clinical trials within 6 months.

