### Intervention

#### Intervention components

We used the transtheoretical model and stages of change (TTM) to guide the intervention strategies in this multi-component lifestyle intervention program. The intervention will be delivered by two trained members of the project through 12 individual biweekly counseling sessions, including 6 face-to-face sessions and 6 telephone sessions, which were tailored to align with key events in routine prenatal care.

The initial 40-minute face-to-face session (10^+ 0^ to 13^+ 6^ weeks) will cover the following topics: definition of EGWG and its adverse effects on maternal and child health, the recommended gestational weight gain based on Chinese references (Table 1) [24], dietary recommendations from the Dietary Guidelines for Chinese Residents [25],“two not, six less” (healthy eating principles: not eating excessively, not drinking sugar-sweetened beverages, eating less fried food, eating less unhealthy snacks, eating less Western-fast food, eating less takeout, eating less high-sugar desserts, and eating less processed meat), weekly physical activity and weight management goals for pregnancy. The biweekly sessions will be performed through telephone or face to face to provide feedback on behavioral changes and weight gain over the past two weeks based on data from the App and wristband, to review behavioral and gestational weight gain goals, and for participants with poor weight control, a detailed discussion of diet and exercise habits to identify key challenges will be provided, followed by tailored guidance.

**Table 1 Tab1:** Recommended gestational weight gain standards for Chinese pregnant women

Pre-pregnancy BMI Category	Total Gestational Weight Gain	1 st Trimester Weight Gain	2nd & 3rd Trimester Weekly Gain
Underweight (BMI < 18.5 kg/m^2^)	11.0 ~ 16.0 kg	0 ~ 2.0 kg	0.46 kg (0.37 ~ 0.56)
Normal weight (18.5 ≤ BMI < 24.0 kg/m^2^)	8.0 ~ 14.0 kg	0 ~ 2.0 kg	0.37 kg (0.26 ~ 0.48)
Overweight (24.0 ≤ BMI < 28.0 kg/m^2^)	7.0 ~ 11.0 kg	0 ~ 2.0 kg	0.30 kg (0.22 ~ 0.37)
Obese (BMI ≥ 28.0 kg/m^2^)	5.0 ~ 9.0 kg	0 ~ 2.0 kg	0.22 kg (0.15 ~ 0.30)

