The intervention will be assisted by mobile health apps and wearable devices. The pregnant women in the intervention group will be equipped with a weight management platform account, a smart wristband (Huawei Wristband 8), a weighing scale, and an Elastic band. Participants will receive in-person training on how to utilize the weight management App of the WeChat Public Account “Population health service platform” and the Wristband. These tools will enable them to access health education resources, track weight gain, monitor dietary behaviors and physical activity, and review feedback about their weight and lifestyle behaviors. Details about the intervention are described in Table 2.

**Table 2 Tab2:** Key intervention components based the smartphone app with the help of wristband

Intervention components	Content
Health education activities	48 articles about weight management during pregnancy are presented in the health education module of the Wechat app, participants are required to read 2 to 4 articles per week from 10^+ 0^ to 35^+ 6^ gestational weeks.
Dietary behavior modification	(1) Dietary goal setting: 8 core dietary goal will be set by the program member according to women’s change intention. The eight eating behavioral goals will be assigned to each participant with two for every 4-week cycle. (2) Dietary behavior monitoring: women will be asked to record the 8 dietary behaviors in the App every week.
Active physical activity	(1) Goal reminding: 150 min MVPA per week, recommending 30 min of aerobic exercise (including brisk walking) 3 times a week and 30 min of resistance exercise 2 times a week; goal of 6000 steps/day) will be shown at the face of the physical activity module. (2) Exercise video providing: a 5 min of Warm-up exercises video, a 30 min of aerobic exercise video and a 30 min of resistance exercise video are provided for women to use. (3) Exercise monitoring: on the one hand, women will be asked to record the physical activity behaviors manually in the app every day, with the function of recording multiple times a day; on the other hand, women’s physical activity will be monitored by wearing a wristband every day, with the function of monitoring heart rate, steps, total physical activity time and different levels of physical activity time. (4) Safety reminding: Articles about how to exercise safety and how to deal with the muscle soreness caused by exercise are provided.

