### Fidelity/quality control of the intervention

Data collection and intervention are performed by two key members of the research team, who know the research protocol well. Two operation manuals according to each hospital’s routine perinatal care process have been developed for implementing and managing the intervention. The manuals describe in detail when, where and what the project staff should do in delivering the intervention. Both of the two project staffs will be required to perform the intervention according to the operation manuals.

During the implementation of this intervention, regular online meetings will be held to report the implementation process and record problems and good experiences will also be shared to facilitate the intervention in the future.

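### The adverse-event section covers only perinatal outcomes from the hospital record, so harms of the exercise programme cannot be compared between arms

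*Protocol article*

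**What the plan says.** All references are to the protocol article.

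- **Adverse events.** The section is a single sentence. It names "The perinatal adverse outcomes, including pregnancy loss, gestational diabetes, pregnancy-induced hypertension, preeclampsia, cesarean delivery, and preterm birth (before 37 weeks"), and gives the EMR as the only source.
- **Intervention components, Table 2.** The weekly activity goal is 150 minutes of moderate-to-vigorous activity, "recommending 30 min of aerobic exercise (including brisk walking) 3 times a week and 30 min of resistance exercise 2 times a week", with a daily step goal and exercise videos. On safety the table says: "Articles about how to exercise safety and how to deal with the muscle soreness caused by exercise are provided".
- **Control group.** Control women receive none of the intervention components.
- **Eligibility and recruitment.** Entry requires "no contraindications to physical activity according to Physical Activity Readiness Questionnaire (PAR-Q").
- **Intervention components, text.** The biweekly sessions are "to provide feedback on behavioral changes and weight gain over the past two weeks", to review goals, and to discuss diet and exercise habits with women whose weight control is poor.
- **Fidelity/quality control of the intervention.** "regular online meetings will be held to report the implementation process and record problems". Two operation manuals are mentioned but not shown.

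**The concern.** The arms differ by a programme that includes regular aerobic and resistance exercise through most of pregnancy. The harms most specific to such a programme are physical ones, such as falls, strains and other musculoskeletal complaints. The plan regards exercise safety as relevant, since it screens for it at entry and gives advice on it. The adverse-event section, however, is drawn around pregnancy and delivery outcomes.

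At stake is what the trial report can say about safety. If the section is followed as written, the report can compare pregnancy loss, preterm birth and the other perinatal outcomes by arm. It can make no comparative statement about harms of the exercise component.

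**Working it through.** The plan gives no figure to reproduce. The check sets the sections side by side and counts.

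**1. Scope of the adverse-event section.** Six outcomes are named: pregnancy loss, gestational diabetes, pregnancy-induced hypertension, preeclampsia, cesarean delivery and preterm birth. The word introducing them leaves the list open, but only within perinatal outcomes. A fall or a musculoskeletal injury does not naturally belong to that class.

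**2. What the section adds to the Outcomes section.** Gestational diabetes, gestational hypertension, preeclampsia and cesarean delivery are already secondary outcomes. That is 4 of 6. The named events that are new are 6 − 4 = 2: pregnancy loss and preterm birth.

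**3. Exposure to exercise.** In the intervention arm the goal is 3 × 30 + 2 × 30 = 150 minutes a week, which agrees with the stated weekly total. The Study design section puts the intervention at about six months. Control women are set no such target.

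**4. Other routes by which an exercise-related harm could be recorded.**

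| Place | What it records | Exercise-related harm? |
|---|---|---|
| Table 3, anthropometric and clinical rows | Weight, blood pressure, body composition, gestational diabetes, hypertensive disorders | No |
| Table 3, questionnaires | Diet, activity, sleep, quality of life, mood, self-efficacy, stage of change | No; the SF-12 is described only as a 0–100 quality-of-life score and would not identify an injury |
| Outcomes, all secondary outcomes | Weight gain rate, pregnancy, delivery, neonatal, behavioural and postpartum outcomes | No |
| App and wristband (Table 2) | Diet, activity, weight, heart rate, sleep; intervention arm only | No |
| Biweekly sessions | Behaviour, weight and goals; intervention arm only | Not stated |
| Online meetings | How implementation is going, and problems met | Not stated; concerns delivery, not participants' harms |

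The number of stated provisions to collect exercise-related harm, in either arm, is zero.

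**5. Comparability.** A harm might still be mentioned in a biweekly session. Because only one arm has these sessions, counts from that source would differ between arms through opportunity to report alone.

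**The case against.** The strongest objection is that this is silence in a condensed article. Definitions, grading and reporting routes for adverse events are often left to the full protocol, and the two operation manuals are not shown. The section does not say that other events will go unrecorded, and it contradicts nothing. This has force against any claim about what staff would actually do. It does not dispose of the point, because the article does not leave the matter open: it has an adverse-event section and states both class and source. That stated scope does not fit the intervention.

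Several stronger readings are tempting, and the documents do not support them.

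- *A reader might infer that adverse events are limited to exactly six.* The list is illustrative. Vaginal bleeding or threatened preterm labour could fall within the open perinatal class, so it is not established that they would be missed.
- *A reader might infer that the plan itself foresees injuries.* It names muscle soreness and exercise safety only. The exclusions for cervical insufficiency and continuous vaginal bleeding stand among general medical exclusions, with no exercise rationale given.
- *A reader might infer that exercise injuries would certainly go unreported.* A serious injury might reach the EMR. What can be said is that no provision to extract or report it is shown.
- *A reader might see the overlap with secondary outcomes as a fault.* It is not. Those outcomes can move either way, and counting them by arm shows harm as well as benefit.
- *A reader might infer that wide use would be recommended on an inadequate safety claim.* The Abstract links wide application to the mobile-health methods and makes no safety claim.

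It is also fair to say that the gravest obstetric consequences are covered, since pregnancy loss and preterm birth are named.

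**Conclusion.** The point holds as a mismatch of scope. Adverse events are confined to perinatal outcomes from the EMR, and no provision shown collects exercise-related harms such as falls or musculoskeletal injury in either arm, although only one arm is given an exercise target. As written, the trial could not compare such harms between arms.

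The effect is on the safety report alone. The primary outcomes, the sample size and the efficacy analyses are untouched. The conclusion assumes that the unshown manuals or full protocol do not already provide for this collection in both arms. If they do, the article needs only a sentence saying so.

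No event rate can be attached. The generic rule of three is tempting: 200 women allocated 1:1 gives 100 per arm, 10% attrition leaves 90, and zero events would give an upper 95% bound of about 3/90 = 3.3%. That presumes complete ascertainment, which neither the EMR of two maternal and child health hospitals nor an open-label self-report item can guarantee. It should not be promised. This is a cheap and worthwhile improvement to the plan.

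**What to change.** In the Adverse events section:

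1. Add attendances or admissions for injury or fall to the EMR extraction already planned for both arms, and state explicitly that vaginal bleeding and threatened preterm labour are extracted.
2. Add one fixed question on injury or musculoskeletal symptoms, worded identically for both arms, to the existing questionnaires at 24+0–27+6 and 32+0–35+6 weeks.
3. Report the counts by arm as descriptive data. Do not draw them from the counselling sessions, which only the intervention arm receives.

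The cost is a few extraction fields and one item at two existing visits, with no new visits or staff. If those visits are already over, the EMR part can still be done retrospectively, but the question cannot.

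Two limits should be stated with the results. Self-report is unblinded and may differ by arm, since only one arm receives the soreness material and regular contact. Injuries treated at other hospitals may be missed. The change concerns data collection only and implies nothing about the exercise programme itself.
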